### Monitoring and ethics

There will be no data monitoring committee. However, data will be regularly monitored (i.e. following each workshop) by the principal investigators. There is no external funding for this study and therefore the principal investigators have no financial or other competing interests. Adverse events during the workshops or within data collection will be logged and reported. The study is approved by the ethics committee of Charité Universitätsmedizin Berlin (No.: EA2/185/19). We have to point out that our ethics approval does not yet cover the implementation of reminders. This aspect is currently being submitted in a supplementary application. We assume that this aspect is ethically acceptable and that a corresponding positive vote can be handed in later. Other protocol amendments are not planned. In case an adjustment to the protocol is necessary, this will be indicated in the subsequent report of our results. By publishing this study protocol in advance as well as by using a study registration, all subsequent changes are traceable. Only the principal investigators of this study will have access to the final datasets. All data will be encoded and stored electronically on a password-protected external drive. All identifiable data (i.e. completed questionnaires) are secured as a single version in lockable cabinets that are in lockable rooms.

Only analyses based on aggregated data (*n* > 15) will be released back to the organization to ensure the anonymity of participants. The invitation to participate in the study will state that participation is voluntary and no negative consequences will impact those that choose not to participate. The overall study results and circumstances will be made available to all individuals irrespective of their group allocation.

## Discussion

We introduced a workshop to increase health-seeking behaviors in office workplaces in Germany. Our workshop is based on a combination of physical activity and health behavior planning.

At first, we want to indicate one minor limitation regarding our data acquisition: we have to validate our PAD. The diary is adapted to a validated questionnaire; however, that questionnaire has not been validated for daily usage. Moreover, the literature showed differences between self-reported (i.e. by questionnaires) and accelerometer-measured physical activity [48, 49]. Therefore, we use accelerometer-measured physical activity to prove our PAD in a sub-sample of our participants. If the result of our analysis shows insufficient validity, only the data from the accelerometry will be used. Another limitation refers to the recruitment process. The participants are recruited in different organizations and therefore have different pre-conditions (i.e. workplace equipment, health services) as well as differently effective health counsellors. Thus, we will collect data on the organization to control for potential experimenter effects between organizations.

In addition, there is some risk of inter-subject group bias if individuals in one group inform a member of the other group about reminders. In the follow-up survey, we will ask the group without reminders whether they received information about the procedure in the other group. We can then perform analyses according to whether participants received information about the other group and exclude them from the analyses, where necessary. Participants of the workshops might be less active in winter. Hence, the season could affect the amount of physical activity. As data of both intervention groups will be collected in the same season, they remain comparable. All these issues could affect our results and should be critically reviewed later.

Regarding the HAPA model, participants have different stages: motivational as well as volitional [28, 29]. Participants at the motivational stage first have to learn the physical activity is beneficial as it is associated with numerous positive effects. At the volitional stage, participants rather need help with the implementation in their daily routines. Our intervention targets both stages: (i) the motivational, as the workshop contains knowledge transfer about positive effects and ways to overcome barriers of physical activity, and (ii) the volitional, as the main contents are the performance of the physical activity and the learning of implementation strategies. A similar study on sedentary behavior used a personalized intervention approach to reduce such behavior [50]. The study failed regarding the sum of sedentary minutes per day but decreased the number of long periods of sedentary behavior. In contrast, another study showed that a multi-component intervention can change sitting times in favor of standing times [14]. As mentioned in the introduction, we use these and other described findings from the literature in our approach to developing optimal support for small and medium-sized companies in Germany.

We also have to look at our workshop critically because of the current pandemic. Currently, in Germany, it is only allowed to meet in small groups concerning the hygienic guidelines, which can limit our onsite workshop. Therefore, other options have to be discussed, for example, a web-based solution with an interactive video function. Such an adaptation is conceivable since our concept and the appropriate content can be easily transferred. A web-based workshop has also other advantages: (i) it is easier to implement in a daily routine, (ii) it is independent of the participants’ location, (iii) the capacity limits depend on a stable internet connection, and (iv) participants learn a web-based interaction that might be beneficial for other work processes. Thus, using a web-based solution as an eHealth tool is advantageous, however, there should be clearly defined rules (i.e. regarding data privacy and data security) for implementation [37]. Besides those rules, a recent study in German and Austrian leaders indicated that eHealth tools should include feedback from experts to increase the acceptance rates of a tool [51]. Another aspect regarding a web-based solution are the insufficient health promotion offers in small- and medium-sized companies in Germany, especially as these companies account for 90% of the entire sector [52, 53]. Web-based services are highly effective in terms of time and costs and could therefore support the implementation of health promotion offers in these companies. Considering all the approaches, our current study could be the first step towards a web-based workshop.

Summing up, our study includes a live workshop based on a multi-component approach that is promising to help increase physical activity in office workers. After data evaluation, we will review our hypotheses and results in line with the mentioned limitations critically. Thereby, we will be able to develop an effective workshop for health promotion that could be implemented at home and office workplaces. Especially a web-based solution, with its potential to reach many people in an increasingly digitalized work environment, will be developed and tested based on our first results.

Possible implementation areas would be the classic workplace and new forms of work, for example, home-office and mobile working.

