**Methods:**

We use a randomized controlled trial with two intervention groups: a live workshop with and without additional reminders. The workshop intervention design consists of a baseline measurement, two workshops, and one follow-up measurement. Each workshop takes place in small groups (*n* < 11). We use a randomized allocation to both groups. To control for health-related effects and the expected behavior change we examine (i) physical activity (i.e. active time, taken steps, etc.) by a tracking device (ii) physical wellbeing, motivation, and volition by an online questionnaire, and (iii) participants also report physical activity by a diary. All measurements are taken one week before the respective workshop and 24 weeks after the initial baseline measures.

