## Methods

### Participants

We recruit office desk workers aged between 18 and 67 years from different organizations (i.e. public administration with standard office workplaces) in Germany. Two intervention lines are planned: one live workshop group with and one without reminders. After attending the first workshop participants in the appropriate intervention group will receive reminders via e-mail twice a week. The e-mails remind the participants of the possibilities to be physical active at the work place previously introduced through the workshop. Overall, eight e-mails will be sent until participants answer the second online survey one month after participating in the workshop. We use a randomized allocation of the participants to both groups. As inclusion criteria, we define an age group between 18 and 67 years and the employee council of each institution has to approve the participation. Additionally, participants are asked not to take part in other studies during the time of the workshop intervention. Participants are excluded if they take part in only one workshop or do not fill in the questionnaires (missing answers > 30%) appropriately. All participants will be informed about the content and objectives of our study, they can ask questions, and they can withdraw from the participation at any time. As a prerequisite for participation, participants of our study sign a declaration of consent. A meta-analysis [38] revealed small intervention effects of workplace physical activity interventions (d = 0.21). Based on this assumption, power-analysis (G-Power 3.1) indicated in sum 168 participants for an ANOVA with repeated measures (within-between interaction). Our calculation included *f* = 0.11, *α* = 0.05, β = .80, three groups, and three measurements.

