### Study-aim and procedure

Our study aims to examine health-related effects from two slightly different live workshops with office workers. Therefore, we contact health counselors at various companies in Germany. If they are interested in participating in our study, further details will be discussed and the employee council and management level will be involved. If the management approves our study, the health counselors will be interviewed and will help to distribute the information among the employees (i.e. via email). In an email, participation in one of our groups will be clearly explained. The study information and the consent form are attached to this email, with additional contact details of the study supervisors (i.e. regarding upcoming questions). As a prerequisite for participation, these documents must be signed and returned. The participants have the opportunity to choose a suitable date from a list of workshop dates in their company. Each participant receives a link to participate in the online questionnaire as well as an activity diary one week before their first workshop. Additionally, we use accelerometers to objectively measure physical activity during this week. Accelerometers with instructions, activity diaries and an online survey will be sent to all consenting participants for data collection. The instructions explain how to attach the accelerometer to the participant’s thigh and hip. Previous studies have indicated three days are sufficient to observe a stable pattern of physical activity [39]. Not wearing the accelerometer for 3 successive days leads to exclusion of the participant from the study.

This procedure is repeated one week before the refresher workshop and after six months. We have no blinding of our workshop supervisors and outcome assessors or data analysts. In each group data collection starts one week before the first workshop. The study procedure is presented in Fig. 1.

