### Intervention

The first workshop lasts about two hours, the refresher workshop only one hour. Each workshop consists of active and passive parts. Table 1 describes the first workshop including active and passive parts. The refresher workshop includes some new activities (see part III in Table 1) as well as an interactive question-answer part. In the latter participants can ask questions about the workshop and further individual strategies, and can discuss adaptations. This concept is used in a live workshop with and without reminders. The reminders are used to retain the acquired contents and knowledge of the first workshop and to give incentives for physical activity.

**Table 1 Tab1:** Description of main contents during the workshop; participants were actively (i.e. physically active) or passively involved

***Part***	***Content***	***Participants’ involvement***
I	Workshop trainers give some general information about inactive lifestyle and behavior (i.e. statistics) at German workplaces and resulting health-related issues (i.e. physically, social, psychological), based on recent studies. Different concepts for increased physical activities at the workplace are shown and participants are asked in anonymized live-questions about their daily physical activity.	passive
II	The trainers give instructions on adequate health safety standards regarding the office desk setting, based on German laws and regulations. This includes the rights & duties as well as the health-related behavior of office workers at their workplace (i.e. position of the desk, equipment, sitting/standing positions) in Germany. Again, the participants are asked for their participation in anonymized live-questions about these topics.	passive
III	Trainers show some exercises from the areas of mobilization, strengthening, and stretching. All examples can be performed at the workplace. At the end of this tryout, some recommendations for physical activity (i.e. how long and often exercises should be performed) are given.	active
IV	Trainers and participants of the workshop discuss opportunities and barriers to daily physical activity in individual group activities. Experiences are shared and the group works on the conception of action plans. Finally, each participant should create his/her plan.	active

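### A single reminder-leakage question at about week 24 cannot date the leakage, so it is a poor basis for splitting or excluding participants at the second measurement

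*Protocol article*

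**What the plan says.** All statements are in the protocol article.

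- **Discussion.** The article names the risk that members of one group tell members of the other about the reminders. The check is: "In the follow-up survey, we will ask the group without reminders whether they received information about the procedure in the other group". It then allows analyses according to the answer, and exclusion of those who were informed if judged necessary. It gives no reference period for the question and does not say which measurement an exclusion would apply to.
- **Abstract, Methods.** The design has "a baseline measurement, two workshops, and one follow-up measurement". On timing: "All measurements are taken one week before the respective workshop and 24 weeks after the initial baseline measures".
- **Participants.** After the first workshop the reminder group "will receive reminders via e-mail twice a week", and "eight e-mails will be sent until participants answer the second online survey one month after participating in the workshop".
- **Study-aim and procedure.** After the baseline week, "This procedure is repeated one week before the refresher workshop and after six months".
- **Intervention.** Both live groups receive the same workshop concept, refresher included. "The refresher workshop includes some new activities (see part III in Table 1) as well as an interactive question-answer part".

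**The concern.** The reminder comparison is observed at two times after baseline: the second measurement, just as the reminders stop, and the 24-week measurement. Leakage matters differently for each. What a participant without reminders hears during the reminder weeks can shrink the difference between groups at both. What that participant hears afterwards can affect only the 24-week difference.

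One undated answer collected at 24 weeks merges the two. Applied to the second measurement, it can go wrong in both directions:

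- someone who heard of the reminders only later is treated as contaminated at a time when they were not;
- someone who heard early and has forgotten is treated as clean.

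At stake is the purpose of the check. If the reminder effect at the second measurement is small, the planned leakage analysis cannot show whether dilution is the reason. Exclusions based on it may remove valid second-measurement data.

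**Working it through.** **1. Which survey is meant.** The Abstract counts a single follow-up measurement, apart from those tied to the two workshops. The Participants section calls the one-month instrument the second online survey. The follow-up survey in the Discussion is therefore most naturally the 24-week one, although the Discussion does not define the term.

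**2. The article's own reminder count.** 8 e-mails / 2 per week = 4 weeks, which agrees with the stated one month. The reminder schedule is internally consistent.

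**3. Timeline** (week 0 = start of the baseline week; one month taken as 4 weeks):

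| Event | Week |
|---|---|
| Baseline | 0 |
| First workshop | 1 |
| Last reminder and second survey | 1 + 4 = 5 |
| Refresher, one week after the second measurement | about 6 |
| Follow-up survey | 24 |

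End of reminders to leakage question: 24 − 5 = 19 weeks. Refresher to leakage question: 24 − 6 = 18 weeks.

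**4. Sensitivity to conventions.**

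- One month as 4.34 weeks: 24 − 5.34 = 18.7 weeks.
- Counting from the first workshop instead of the baseline week: 24 − 4 = 20 weeks.
- Reading six months as 26 weeks: 26 − 5.34 = 20.7 up to 26 − 4 = 22 weeks.

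The gap is 18.7 to 22 weeks on every reading, and the question always falls after the refresher.

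**5. What a yes can mean.**

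| Information received | Can affect second measurement | Can affect 24 weeks | Answer at week 24 |
|---|---|---|---|
| Weeks 1–5 | yes | yes | yes, or no if forgotten |
| Weeks 5–24 | no | yes | yes |
| Never | no | no | no |

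The first two rows give the same answer but differ at the second measurement. Recall of the reminder phase spans 24 − 5 = 19 to 24 − 1 = 23 weeks. Asked at the second survey, it would span 0 to 4 weeks.

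**6. Can the misclassification be sized?** Among yes answers, the share that is wrong for the second measurement is late / (early + late), where both are proportions of the group without reminders and recall is taken as perfect. The article gives neither. Assuming 10% early leakage:

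- late 2%: 2 / 12 = 17%
- late 5%: 5 / 15 = 33%
- late 20%: 20 / 30 = 67%
- late 40%: 40 / 50 = 80%

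The result runs from 17% to 80% on the assumed late share alone, so the documents fix no size.

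**The case against.** **Item wording.** The case against rests mainly on the article being condensed. The Discussion gives one sentence of intent; the actual item might ask when the information came, and the full protocol may hold that wording. This stands in part: the documents show that misclassification can occur, not that it will. But the article does state when the question is asked and what the answer may be used for, and that combination can be criticised as written.

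**Week 24 is an outcome too.** The Statistics section plans repeated-measures analyses, and the sample size assumes three measurements. Later leakage is relevant to the last of these, and only a late question can catch it. This stands. A reader might infer that the late question is useless or that only the second measurement matters; the documents support neither. The late question should stay, but it cannot do both jobs.

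**The refresher as a route.** A reader might infer that the groups mix at the refresher and exchange information there. The article says only that participants choose a date within their company, and describes questions on the workshop and individual strategies, not on reminders. Mixing is possible but undocumented. The argument does not need it: leakage after week 5 by any route is enough.

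**Exclusion is optional.** The text permits exclusion and does not commit to it. This stands, and it lowers the weight of the point.

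**Loss of power.** A reader might wish to attach a power loss. Take 168 / 3 = 56 per group (equal split assumed), 10% early and 20–40% late leakage, all yes answers dropped, and a two-sample t-test. Compared with dropping early leakage only, power falls from 0.72 to 0.66–0.57 at an assumed 0.5 SD. At the article's planning effect of d = 0.21 it falls from 0.19 to 0.17–0.15, about 2–4 points. With 2–5% late leakage, power at 0.5 SD is 0.72–0.71, essentially unchanged. The leakage shares and the 0.5 SD are not in the documents, and the t-test is not the analysis the trial was sized for. None of these figures can be put forward as the cost.

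**Conclusion.** The point holds in a limited form and is minor. If the follow-up survey is the 24-week survey, the leakage question comes about 19 weeks after the reminders end (18.7 to 22 across conventions) and after the refresher. As described, it cannot tell leakage in weeks 1–5 from later leakage. Using the answer to split or exclude participants can therefore misclassify them at the second measurement, in either direction. The extent is unknown.

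The conclusion rests on two assumptions: that reading of the term, and an item that asks whether but not when. If the second survey was meant, the article need only say so, and the timing objection falls for that measurement.

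A related weakness would remain after any change of timing. The answer arises after randomisation and is collected in one group only, so excluding on it breaks the randomised comparison.

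**What to change.** 1. Add the leakage item to the existing second survey (about week 5, before the refresher), and use that answer for the second-measurement contrast.
2. Keep the item at week 24, asking whether the information came before or after the refresher, and use that answer for the 24-week contrast.
3. Keep all randomised participants in the main analysis regardless of the answer. Use exclusion by leakage status only as a sensitivity analysis, and replace the open-ended condition for exclusion with that rule.
4. State in the Discussion which survey is meant.

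**Cost.** One planned question is asked twice in surveys that already exist, and the article states that the study has not yet started. The downside is that asking at the second survey may hint at the reminders a week before the refresher, while the 24-week outcome is still to come. Neutral wording keeps this small, and the invitation e-mail described under Study-aim and procedure already explains participation in the groups.

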The participation should motivate and offer new perspectives of increasing physical activity at the workplace. We have also designed the workshop in such a way that our concept can be used in various companies. In this first step, we want to prove our concept in medium-sized organizations. Due to the current pandemic situation, there is an increasing number of people working in separate offices without any contact with other co-workers. To ensure that these changes do not lead to increased inactivity, new work-related health offers or activity programs should be established. We developed a workshop which takes all the above-mentioned points into account. The use of computer prompts combined with providing information reduces sitting time on average by 14 to 96 min per day*.* In this early stage, we want to prove the concept of our live approach in small groups and hypothesize that the participants show positive health effects (i.e. well-being, decreased MSD) and positive adaptations in their health behavior (i.e. increased physical activity). We hypothesize that additional reminders improve health-related effects. In addition, we want to develop our workshop design in the framework of eHealth applications or a web-based solution, since the integration of such approaches might improve the efficiency of health programs at work [37].

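### Participants in the no-reminder group alone may be dropped after follow-up for having heard about the other group, with no criterion, which can bias the reminder comparison in either direction

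*Protocol article*

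**What the plan says.** Allocation is random (Methods, Participants): "We use a randomized allocation of the participants to both groups". The comparison at issue rests on a hypothesis in the Introduction: "We hypothesize that additional reminders improve health-related effects".

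Among the limitations in the Discussion, the authors recognise that members of one group may tell members of the other about the reminders. Their response has two parts. First, "In the follow-up survey, we will ask the group without reminders whether they received information about the procedure in the other group". Second, "We can then perform analyses according to whether participants received information about the other group and exclude them from the analyses, where necessary".

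On blinding, Study-aim and procedure states: "We have no blinding of our workshop supervisors and outcome assessors or data analysts". Under Monitoring and ethics, the principal investigators review data after each workshop and are the only people with access to the final datasets. The Statistics section covers missing values, outliers, repeated-measures analyses and the significance level. It does not mention or limit this exclusion.

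**The concern.** Having heard about the other group is a characteristic that arises after randomisation. It is recorded in one arm only, so those removed from the no-reminder arm have no identified counterparts in the reminder arm. Once they are removed, randomisation no longer guarantees that the two sets of participants are comparable. If the informed would have changed more or less than their colleagues in any case, that difference enters the estimated reminder effect.

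The exclusion is also left to judgement. The text does not define how much information counts, what makes exclusion needed, or which analysis it applies to. The answers arrive at follow-up, and the people deciding may know both allocation and outcomes. An exclusion made under this sentence would not count as a departure from the protocol, so the undertaking to report protocol adjustments would not necessarily bring it to light.

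**Working it through.** **1. The plan's own figure.** Inputs from Participants: f = 0.11, α = 0.05, power 0.80 (printed as β), three groups, three measurements, total N = 168. For the within-between interaction, λ = f²·N·m/(1−ρ), df1 = (k−1)(m−1), df2 = (N−k)(m−1). The article does not state ρ or ε, so ρ = 0.5 and ε = 1 are assumed. Then λ = 0.0121 × 168 × 3 / 0.5 = 12.2, df1 = 4, df2 = 330, and power is 0.803. The smallest balanced N reaching 0.80 is 168, so the sample size reproduces and this point does not turn on it. An equal split, also an assumption, gives 168/3 = 56 per group.

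**2. Size of the possible shift.** Assume no true reminder effect. Let r be the correlation between the analysed outcome (change over time) and a latent, normally distributed tendency to be informed. Let p be the share of the no-reminder arm that is informed and excluded. The remaining members of that arm have mean −r·φ(z₁₋ₚ)/(1−p), so

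shift (reminder minus no-reminder) = r·φ(z₁₋ₚ)/(1−p), in SDs of the analysed outcome.

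For example, p = 20% and r = 0.3 gives 0.3 × 0.280 / 0.8 = 0.105.

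| p excluded | r = 0 | r = 0.2 | r = 0.3 | r = 0.5 |
|---|---|---|---|---|
| 10% | 0 | 0.039 | 0.058 | 0.097 |
| 20% | 0 | 0.070 | 0.105 | 0.175 |
| 30% | 0 | 0.099 | 0.149 | 0.248 |

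Negative r gives the same values with the sign reversed.

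**3. Effect on false positives.** Simulation used 56 per arm before exclusion, a two-sided t-test at 0.05 on one normally distributed outcome (read here as the change score), and 20,000 runs. Type I error was 0.080 at p = 20%, r = 0.3; 0.111 at p = 30%, r = 0.3; 0.222 at p = 30%, r = 0.5; and 0.050 at p = 30%, r = 0.

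**4. Scale.** The article's planning effect is d = 0.21. If two measurements correlate at 0.5, the SD of change is SD × √(2 × (1−0.5)) = SD, so the two scales then coincide. On that footing 0.039 to 0.248 is about 19% to 118% of 0.21 (0.039/0.21 and 0.248/0.21). The comparison is only a yardstick, because 0.21 refers to workplace physical activity interventions in general and not to adding reminders to a workshop.

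**5. Meaning of r.** If r were instead the direct (point-biserial) correlation between the yes/no answer and the outcome, the shift would be r·√(p/(1−p)). At p = 20% and r = 0.3 this is 0.3 × √0.25 = 0.15, against 0.105 above. The table applies only to the latent-normal definition.

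**The case against.** The strongest reply is that the sentence permits exclusion and does not announce it. It stands among the limitations, and its first half describes an analysis by contamination status, which is close to a sensitivity analysis. Whether exclusion belongs to a main or secondary analysis is commonly settled in an analysis plan, which is not shown. This stands to the extent that exclusion is possible, not certain. It does not remove the point, because the sentence is the article's only stated handling of contamination and it authorises removal without a criterion.

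Questioning one arm is reasonable in itself, since learning about reminders can contaminate only people who do not receive them. The difficulty lies in excluding people on the answer.

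The planned test concerns change over time, so a stable difference between informed and uninformed people that is already present at baseline largely cancels. This also stands. Only an association with change matters, and r is defined accordingly.

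A reader might infer more than the article supports:

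- **That the exclusion favours reminders**, because people who talk to colleagues are more engaged. This is plausible but undocumented. Being informed may reflect a shared office or chance, and the sign could be the opposite.
- **That nearly all of the no-reminder group would be caught**, because of the statement "All participants will be informed about the content and objectives of our study". The follow-up question concerns the other group's procedure and follows a remark about disclosure between participants. How people would answer is unknown.
- **That the exclusion shrinks an already smaller arm.** No allocation ratio is stated.

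**Conclusion.** The point holds as a conditional one. The article allows participants to be removed after randomisation from one randomised arm, without a criterion or analysis status, by analysts who are not blinded. That can bias the reminder versus no-reminder comparison. With no true effect, p = 10–30% and r = 0.2–0.5 under the latent-normal definition, the shift is about 0.04–0.25 SD of the analysed change. It is zero at r = 0 and reverses for negative r. Both p and r are assumptions, since the article gives neither.

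The text does not support saying that the comparison will be biased, or that the bias would run toward a reminder benefit. The article should still be corrected on this point, because the selection can be avoided altogether.

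**What to change.** Replace the closing clause of the Discussion sentence, which permits exclusion, with three statements:

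- In the main reminder comparison no participant is excluded for having heard about the reminders; each is analysed in the allocated arm.
- The proportion of the no-reminder group reporting such information is given descriptively.
- Any analysis that leaves these participants out is a labelled sensitivity analysis. Its definition of being informed and its exclusion rule are fixed before outcome data are seen, and its report notes that it no longer compares groups as randomised.

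The cost is wording only, as Data Availability says the study has not started. The one downside is that contamination, if it occurs, may dilute the estimated reminder effect toward zero.

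This edit alone does not keep every randomised participant in the analysis. The exclusions for attending only one workshop or for more than 30% missing answers (Participants), and for not wearing the accelerometer for three successive days (Study-aim and procedure), are separate and need their own consideration.
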